#### Shape/Texture Identification (STI™) test

This is to measure the ability to identify shapes (cube, cylinder, and hexagon) and textures (one, two, or three dots in a row) in decreasing sizes [31] (www.sensory-test.com). The scores range from 0 to 3 points per hand for each subtest with a maximum score of 6 points. STI™ has been shown to have high test-retest reliability in persons with mild to moderate disability after stroke [25].

#### Fugl-Meyer Assessment—upper extremity (FMA-UE; sensory section)

This is to measure light touch and proprioception of the UL after stroke [32]. The score ranges from 0 to 4 points for each subtest with a maximum score of 8 points per hand. It has been shown to be a clinically useful and a robust instrument in persons with sensory impairments after stroke [33].

#### Tactile object identification test

This is to measure the ability to identify different objects without vision. The test is based on the original test by Yekutiel and Guttman [17]. Out of 20 objects, 15 are used during the assessment. Within 15 s, the participant should blind-folded recognize an object. A correct answer yields 2 points, recognition of some features of the object yields 1 point, and an incorrect answer yields 0 point, yielding a maximum total sum score of 30 points.

### Secondary outcome measures

#### Box and Block Test (BBT)

This is to assess gross manual dexterity. It consists of a box with two compartments and of 100 wooden blocks. The number of blocks that can be transported from one compartment to the other during 1 min is counted [34]. The BBT has been shown to be reliable in persons with mild to moderate disability after stroke [35].

#### The mini Sollerman Hand Function Test (mSHFT)

This is to assess fine manual dexterity (PROcare ApS, www.procare.dk). It consists of three selected tasks from the original Sollerman test of 20 items [36]: (1) picking up four coins from a purse, (2) putting four nuts on bolts, and (3) buttoning four buttons. The score ranges from 0 to 4 points for each task with a maximum score of 12 points. The mSHFT has been shown to be reliable in persons with mild to moderate disability after stroke [35].

#### Modified Motor Assessment Scale (M-MAS) of the UL

This is to assess dexterity by five tasks in the advanced hand activity domain. The scale ranges from 0 to 5 points, where 0 represents no motor function and 5 represents almost normal or normal motor function. The M-MAS is a further development of the Motor Assessment Scale [37] and has been shown to have good reliability and validity after stroke [38].

#### Grippit

This is to measure isometric grip strength using a computerized wireless dynamometer (http://www.catell.se). The highest isometric contraction of three trials is recorded in newtons (N). The Grippit has been shown to be reliable in persons with mild to moderate disability after stroke [39].

#### Motor Activity Log (MAL)

This is to assess the participants’ perception of how much (amount of use (AOU)) and how well (quality of movement (QOM)) they use their affected hand in daily activities. The MAL consists of 30 items where the response options range from 0 to 5 for both AOU and QOM, each yielding a score of 150 points. The MAL has been shown to be reliable after stroke [40].

#### Canadian Occupational Performance Measure (COPM)

This is to identify the participants’ problems in their execution of activities in self-care, productivity, and leisure activities [41]. The self-perceived performance and satisfaction of their sensory-related problems are rated on a scale ranging from 1 (do not perform well and not satisfied) to 10 (perform extremely well and extremely satisfied). COPM has shown moderate to good test-retest reliability in persons with stroke [42].

#### Stroke Impact Scale (SIS) participation domain

This is to assess the participants’ perceived participation. The domain consists of eight items, where each item ranges from 5 (limited none of the time) to 1 (limited all of the time). The mean value for the items is calculated and converted into a percentage value from 0 to 100. SIS has shown to be reliable, valid, and sensitive to change in persons with mild to moderate stroke [43].

#### Life Satisfaction checklist

This is to measure perceived life satisfaction by one global item (“Life as a whole”) and ten domain-specific items [44]; in this study, only the global item will be used. The rating ranges from 1 (very dissatisfied) to 6 (very satisfied).

### Data analysis

Descriptive statistics (mean (SD) or median (minimum–maximum)) will be used to characterize the study groups. As this is a new treatment approach, no power calculation can be performed. However, 30 participants can be considered sufficient to include in a pilot RCT within a reasonable time frame. To analyze potential differences between the groups, the Mann-Whitney test (for ordinal data) or independent sample *t* test (for continuous data) will be used. The Wilcoxon signed-rank test or paired *t* test will be used to analyze within-group differences. The level of statistical significance will be set at *p* ≤ 0.05. All calculations will be performed using IBM SPSS Statistics version 22 (IBM Corporation, Armonk, NY, USA).

The interviews of the participants in the sensory group at the 3-month follow-up will be recorded and transcribed verbatim. Data will be analyzed with an inductive content analysis approach [45].

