## Methods/design

### Study design

This is a single-blinded pilot RCT with two treatment arms. Thirty persons with sensory impairments of the UL after stroke will be recruited and randomized either to sensory re-learning in combination with task-specific training (*n* = 15) or to task-specific training only (*n* = 15). In the flow chart (Fig. 1) and the SPIRIT figure (Fig. 2), the overall study design is described, which is in agreement with the SPIRIT checklist (see Additional file 1).

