### Randomization

After the baseline assessments when it has been confirmed that the persons fulfil the inclusion criteria, they will be randomly assigned by sealed paper envelopes either to the sensory group (*n* = 15) or to the control group (*n* = 15) by a person not involved in the training.

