### Outcome measures and assessors

To be able to evaluate the effects of interventions, outcome measures with good psychometric properties will be used, covering different domains of the International Classification of Functioning, Disability and Health (ICF) [28]. Two occupational therapists, who are blinded to the group allocation and with long experience of stroke rehabilitation and the outcome measures used, will conduct all assessments pre- and post-training and at 3-month follow-up. At the 3-month follow-up, the participants in the sensory training group will also be interviewed regarding their experiences and perceived effects of the training by an interviewer not involved in the training.

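### The planned between-group tests cannot use the pre-training score that is measured for every outcome; they stay valid on average but give up precision and leave the estimate open to chance baseline imbalance.

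*Protocol article*

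**What the plan says.** The Data analysis section names one pair of methods for comparing the arms: "To analyze potential differences between the groups, the Mann-Whitney test (for ordinal data) or independent sample" t test for continuous data. It mentions no covariate, regression model or other adjustment. Apart from describing the groups, the only analysis given to the baseline values is within each arm: a Wilcoxon signed-rank or paired t "test will be used to analyze within-group differences". That analysis does not compare the treatments.

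The baseline scores exist for every outcome. Under Outcome measures and assessors, the blinded occupational therapists "will conduct all assessments pre- and post-training and at 3-month follow-up". The Randomization section puts allocation, which uses sealed envelopes, at a later point: "After the baseline assessments when it has been confirmed that the persons fulfil the inclusion criteria". The pre-training score is therefore unaffected by treatment and is a proper covariate.

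The trial is small. Study design states that "Thirty persons with sensory impairments of the UL after stroke will be recruited and randomized", with 15 in each arm. The article does not say whether the between-group tests are run on post-training scores or on change from baseline.

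**The concern.** Participants are at least 6 months past their stroke and can enter with any score from 0 to 5 on the 0-to-6 STI test, itself a primary outcome. Their starting levels can therefore differ widely, and where a score tracks its own baseline, part of the spread after training is already known before allocation. A test that cannot use the baseline leaves that spread in the error term.

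At 15 per arm, noticeable baseline gaps between the groups will also occur by chance. How a gap carries into the result depends on the choice the article leaves open: post scores carry part of it forward, and change scores subtract too much of it. The two readings differ by the whole baseline gap, and either would fit the current wording.

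This is not a detail merely left to an analysis plan. The article names the tests, and the named tests cannot adjust. The stated purpose is to find out whether the combined training is more effective, tested at the 0.05 level, and the results are meant to inform the design of a larger trial.

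**Working it through.** There is no planned figure to reproduce: the article says that no power calculation can be performed and gives no effect size or SD. For scale, 15 per arm at two-sided 0.05 gives an unadjusted t test 80% power for a difference of about 1.06 SD (noncentral t, 28 df).

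**Inputs from the article:** 15 per arm (Study design, Randomization); significance level 0.05 (Data analysis).

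**Assumed:** two-sided testing; no dropout; a true difference of 0.8 SD; equal SDs before and after training; pre/post correlation r of 0.3, 0.5, 0.7 or 0.8. None of these is in the article.

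**Step 1: size of a chance baseline gap.** The difference between two baseline means has standard error √(2/15) = 0.365 SD.
- P(gap > 0.5 SD) = 2 × [1 − Φ(0.5/0.365)] = 17%
- P(gap > 0.3 SD) = 2 × [1 − Φ(0.3/0.365)] = 41%

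**Step 2: what a 0.5 SD gap does to the estimate.** The shift is r × 0.5 for post scores, (r − 1) × 0.5 for change scores and 0 for ANCOVA.
- r = 0.5: +0.25 SD and −0.25 SD
- r = 0.7: +0.35 SD and −0.15 SD

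**Step 3: variance of the group difference, relative to a post-score t test.**
- Post scores: 1
- Change scores: 2(1 − r)
- ANCOVA: (1 − r²) × (1 + 1/26), where 1/26 = 1/(2 × 15 − 4) is a small-sample allowance

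**Step 4: power.** The noncentrality is 0.8/√V × √(15/2), with V from step 3, on 28 df (27 for ANCOVA). For post scores it is 0.8 × 2.739 = 2.19, giving 56%. For ANCOVA at r = 0.7 it is 0.8/√0.530 × 2.739 = 3.01, giving 83%.

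| r | V, change | V, ANCOVA | Power, post | Power, change | Power, ANCOVA |
|---|---|---|---|---|---|
| 0.3 | 1.40 | 0.945 | 56% | 43% | 58% |
| 0.5 | 1.00 | 0.779 | 56% | 56% | 67% |
| 0.7 | 0.60 | 0.530 | 56% | 78% | 83% |
| 0.8 | 0.40 | 0.374 | 56% | 92% | 93% |

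**Step 5: the same gain in participants.** ANCOVA with 15 per arm matches a post-score test with 15/V(ANCOVA) per arm: about 16, 19, 28 and 40 at the four values of r. It matches a change-score test with 15 × V(change)/V(ANCOVA) per arm: about 22, 19, 17 and 16.

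**Step 6: false positives given an imbalance.** With post scores, no true effect and a baseline gap of exactly 0.5 SD, the approximate chance of a significant result is 4.8%, 5.8%, 6.3% and 5.6% at the four values of r.

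**The case against.** The planned tests are conventional and valid. Randomization makes the unadjusted comparison unbiased on average and controls the type I error, and the 17% chance of a large gap is already part of the test's sampling distribution. This stands. A reader might infer that the analysis is the only protection against imbalance, or that imbalance would readily produce false positives. The documents do not support that: allocation is randomized, and step 6 stays close to 5%. Nor can the article's silence on stratification be held against it, since a condensed article may leave that out.

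The gain may also be small. If change scores are what is meant, ANCOVA adds 5 points of power at r = 0.7 and 1 point at r = 0.8. If r is 0.3, it adds 2 points over post scores. This stands too. A reader might infer that ignoring baseline roughly halves the information; that holds only for post scores with r near 0.7 (15 per arm doing the work of 28). A reader might also take baseline severity to be the largest source of variation in these scales, but nothing in the article says so.

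It might be argued that change scores clash with choosing a rank test for ordinal data. That argument is weak, because the plan's own Wilcoxon signed-rank test already works with differences of such scores.

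Finally, this is a pilot without a power calculation. That lowers the weight of lost power but does not remove the point, since the aim is a between-group comparison of effectiveness with a significance test.

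**Conclusion.** The point holds as a should-fix matter of efficiency, not as a flaw in validity. The article commits to between-group tests that cannot use a pre-randomization score available for every outcome. ANCOVA is more precise than either possible reading at every correlation examined, and it makes the unstated choice between post and change scores unnecessary.

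The size of the gain is a range, because r is assumed. Against post scores it is negligible at r = 0.3 and material from about 0.5. Against change scores it is largest at low r and nearly gone at 0.8. The conditional bias matters only if a sizeable gap occurs.

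All power figures are normal-theory. The four primary outcomes are bounded scores, at least two of them short (STI 0 to 6, FMA-UE sensory 0 to 8), so for these the figures show direction and rough scale only.

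**What to change.** In the Data analysis section, state that for each outcome and visit the primary between-group comparison adjusts for the pre-training score of the same outcome, as follows:

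- **ANCOVA**, reporting the adjusted mean difference with its 95% CI, for BBT, Grippit and the longer sum scores: monofilament (0 to 25), tactile object identification (0 to 30), MAL and SIS participation.
- **Rank ANCOVA on the baseline rank** for the short ordinal scales: STI, FMA-UE sensory, mSHFT, M-MAS, COPM and life satisfaction. Report its p value with descriptive group medians, because the method does not give a difference in score units.
- **The Mann-Whitney and t tests** kept as sensitivity analyses, stating whether they use post-training or change scores.

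The change should be made before any unblinded analysis. It needs no extra visits, participants or measurements. It costs one degree of freedom per model and slightly more analysis work.

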The purpose of this pilot randomized controlled trial (RCT) is therefore to investigate if sensory re-learning in combination with task-specific training may prove to be more effective than task-specific training alone to improve sensation of the hand (primary outcome), dexterity, ability to perform daily hand activities, perceived participation, and life satisfaction (secondary outcomes). The results from this study can provide information on how to design a fully powered RCT in the future.

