### Inclusion of participants

Potential participants will be identified and recruited by physiotherapists and occupational therapists from the Department of Neurology and Rehabilitation Medicine, Skåne University Hospital or from two outpatient health care settings specialized in stroke rehabilitation. Inclusion criteria are as follows: sensory impairments (≤5 points in the Shape/Texture Identification test [25]) of the UL after stroke, ability to grasp and release an object, ability to understand oral and written information, 18–80 years of age, at least 6 months since stroke onset, and ability to walk with or without an assistive device. Exclusion criteria are as follows: sensory impairments in the UL due to other diagnoses than stroke.

First, a letter with information about the study will be mailed to potential participants. One to 2 weeks later, they will be contacted by phone and asked if they are interested in participating in the study. Additional questions about their sensory-related problems of the UL in daily life will also be asked. Eligible and interested participants will then be assessed at the Department of Neurology and Rehabilitation Medicine.

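### Within-arm significance tests are planned at the same p ≤ 0.05 as the between-group tests, with no stated role, although they cannot show that one training is better than the other

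*Protocol article*

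**What the plan says.** The Background section sets a comparative aim, namely whether "sensory re-learning in combination with task-specific training may prove to be more effective than task-specific training alone". The Data analysis section gives the comparative test first: "To analyze potential differences between the groups, the Mann-Whitney test (for ordinal data) or independent sample *t* test (for continuous data) will be used". The next sentence adds tests within each arm: "The Wilcoxon signed-rank test or paired *t* test will be used to analyze within-group differences". A single criterion follows, "The level of statistical significance will be set at *p* ≤ 0.05", with no distinction between the two kinds of test. The section also states "As this is a new treatment approach, no power calculation can be performed", so no effect size or SD is given. The study is planned with 15 participants in each arm (Study design; Randomization).

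Two further places bear on the STI test, which is one of the four primary measures. Eligibility requires "sensory impairments (≤5 points in the Shape/Texture Identification test [25]) of the UL after stroke", on a scale whose maximum is 6. Allocation follows "After the baseline assessments when it has been confirmed that the persons fulfil the inclusion criteria", so the qualifying score is obtained no later than the baseline assessment and before randomization.

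**The concern.** A paired test inside one arm asks whether that arm changed. The trial asks whether one arm changed more than the other. Both arms receive active training, and the Background itself says that task-specific training can improve motor performance, so change in both arms is plausible, most clearly for the motor outcomes. When both arms truly change by the same moderate amount and each has only 15 participants, each within-arm test has an intermediate chance of significance. It is then easy for one arm to cross 0.05 and the other to miss it.

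That pattern reads as evidence for the sensory training but is not a test of it. The Discussion section makes the design of a larger trial depend on whether the approach proves efficient, so a within-arm result read in this way could misdirect that decision.

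**Working it through.** **Inputs from the protocol article.** n = 15 per arm (Study design; Randomization). Significance level 0.05 (Data analysis), taken as two-sided because no side is stated. The plan gives no power, effect size or SD, so there is no figure of its own to reproduce.

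**Assumption.** Both arms have the same true change d, expressed in SDs of change, so there is no difference between arms. The range d = 0 to 1.0 is shown.

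**Step 1: chance of significant improvement in one arm.** For a paired t test with n = 15, w(d) = P(T > t[0.975; 14 df]), where T is noncentral t with 14 df and noncentrality d√15.

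**Step 2: chance that only the sensory arm is significant.** The arms are independent, so this is w(1 − w).

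| d | w | w(1 − w) |
|---|---|---|
| 0 | 0.025 | 0.024 |
| 0.2 | 0.108 | 0.096 |
| 0.3 | 0.190 | 0.154 |
| 0.4 | 0.303 | 0.211 |
| 0.5 | 0.438 | 0.246 |
| 0.54 | 0.495 | 0.250 |
| 0.6 | 0.580 | 0.244 |
| 0.8 | 0.821 | 0.147 |
| 1.0 | 0.949 | 0.048 |

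For example, at d = 0.5: 0.438 × 0.562 = 0.246. The product w(1 − w) cannot exceed 0.5 × 0.5 = 0.25, whichever within-arm test is used. With the paired t test and n = 15 the maximum falls at d = 0.5435.

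**Step 3: the between-group test in the same setting.** In 20,000 simulated trials at d = 0.54, only the sensory arm was significant in 24.9%. The independent-samples t test on change was significant in 4.97%, which is about 2.5% in favour of the sensory arm. Of the trials in which only the sensory arm was significant, about 9% had a between-group p ≤ 0.05. The two analyses therefore usually disagree in exactly the trials that would look most persuasive.

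**Step 4: selection on STI.** Two STI readings with no true change were simulated: a latent normal score, rounded and limited to 0–6, keeping people whose first reading was 5 or less. The protocol calls STI reliability high but gives no coefficient, so the inputs are assumptions: population mean 2–5, SD 1.5–2.0, latent reliability 0.70–0.95.

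- The mean apparent gain was 0.00 to 0.32 points.
- The rate of false significant improvement per arm (paired t, n = 15) was 2.5% to about 14%, against a nominal 2.5%. With latent reliability of 0.90–0.95 it was about 2.5% to 8%.
- With mean 2 and SD 1.5, where about 1% of candidates score 6, the rate stayed at 2.5–2.7%. The high values arise with mean 5, where 37–40% score 6.

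Eligibility is confirmed before allocation, so this gain is the same in expectation in both arms and cancels in the comparison between them.

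**The case against.** The strongest reply is that the plan proposes no misuse. Between-group tests are planned and listed first, the aim is comparative, and the within-arm tests are described as addressing only within-arm differences. A reader might infer that the authors mean to conclude superiority from within-arm p-values, but no sentence says so. This part of the reply stands. What remains is that inferential tests which cannot address the aim are expressly planned, under the same criterion as the tests that can. That is stated text and not a detail left to an analysis plan.

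A reader might also take 25% as the expected error rate. It is an upper bound per outcome and time point. The rate is 2.4% with no change and 4.8% at 1.0 SD. Equal moderate change is also less obvious for the sensory primary outcomes, because the control training has no sensory focus and participants are at least 6 months past their stroke.

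A reader might infer that selection on STI inflates all the within-arm tests. It acts directly on STI only. The cut-off removes only the top score, and the size of the effect rests on assumed inputs.

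Finally, describing change within each arm is ordinary and useful in a pilot trial. That is right, but estimates with intervals serve this purpose without p-values.

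**Conclusion.** The point holds in a limited form. The plan applies p ≤ 0.05 to within-arm tests that do not compare the arms, and gives them no descriptive label. If the true change is equal in both arms, a finding that only the sensory arm improved occurs by chance in 2.4% to 25% of trials per outcome and time point, for common changes from 0 to 1.0 SD. The between-group test gives about 2.5% in that direction. The 25% bound needs an assumed common change of about 0.54 SD with 15 per arm. The intermediate values assume a paired t test, two-sided 0.05 and independent arms.

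Regression to the mean is a side issue for STI only: probably modest, near zero if few candidates score 6, and no source of bias between the arms. The documents do not support the reading that the planned between-group analysis is invalid or that superiority will be judged within arms.

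**What to change.** In the Data analysis section, replace the within-group Wilcoxon signed-rank and paired t tests with a descriptive report of change in each arm (mean or median) with 95% CI and no significance test. Add one sentence stating that any conclusion on effectiveness rests only on the between-group comparison. Preferably, adjust that comparison for the baseline value of the outcome, which is already collected; this is an improvement and not a condition for resolving the point.

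The cost is small. Within-arm p-values are no longer reported, and the baseline adjustment, if adopted, adds a little analysis work. No further data, visits or participants are needed.
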